### Interventions

The patients of the HBOT group will be evaluated upon admission, after 10, 20, 30 and 35 HBOT sessions and after 6 months and 1 year, and the control group will also be assessed at equivalent periods (upon admission, after 2, 4, 6 and 7 weeks, 6 months and 1 year) to clinically evaluate the ulcers and perform specific measures using the software ImageJ, developed at the National Institutes of Health (NIH, Bethesda, Maryland). HBOT sessions will be held 1 week after randomization. The sessions will be supervised by doctors trained in hyperbaric medicine by the Brazilian Society of Hyperbaric Medicine (SBMH). The HBOT sessions will be conducted 5 days a week, being carried out with patients in a multiplace chamber at 2.5 atm absolute (ATA) and 100% O_2_, with 10 min for compression and decompression, effective sessions of 90 min, with intervals of 5 min for each 30 min of treatment. The dressings will be done in both groups with Exufiber foam Ag® (*Molnlycke*, Gotemburgo, Suécia) or Mepilex® (*Molnlycke*, Gotemburgo, Suécia), which will be chosen according to the characteristics of wounds, with silver dressings for the infected injuries and a foam with polyurethane protective layer for wounds in which granulation tissue has formed. Secondary dressings will be changed daily and the primary dressings (coverings—Exufiber foam Ag or Mepilex) will be changed every 3–5 days, as needed and in both groups. The progression of the wounds and specific treatment, such as appropriate bandage, antibiotic therapy or need of some surgical intervention, will be evaluated on a weekly basis. In both groups, a vascular surgeon will monitor the patients, and who will assess the need for surgical procedures (debridement and amputations), in addition to appropriate antibiotic therapy for each case. With regard to load relief, patients in both groups will wear orthopaedic Baruk shoes.

The SF-36 quality of life questionnaire will be filled upon admission and after 3 months of follow-up in both the groups. Laboratory examinations, such as a haemogram, erythrocyte sedimentation rate, levels of C-reactive protein, creatinine, fasting blood glucose and glycosylated haemoglobin will also be estimated only on admission.

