**Methods:**

A non-blind randomized clinical study will be conducted in the city of Imperatriz, Maranhão state, Brazil, from 2019 to 2020, in diabetic patients with chronic foot ulcers (classified as Wagner grades 2, 3 and 4, persisting for more than 1 month). The outpatient follow-up for diabetic foot patients will be done at the Unified Health System, with a sample size of 120 patients (the randomization allocation will be 1:1, being 60 patients for each arm). Half of the patients will receive standard treatment, i.e. dressings, debridement, antibiotics and load relief, along with HBOT (HBOT group), and the other half will receive only standard treatment (control group). The patients of the HBOT group will be evaluated upon admission, after 10, 20, 30 and 35 HBOT sessions, and after 6 months and 1 year. The patients of the control group will also be evaluated at equivalent periods (upon admission, after 2, 4, 6 and 7 weeks, 6 months and 1 year). The SF-36 quality of life questionnaire will be filled upon admission and after 3 months of follow-up in both groups. The primary and secondary endpoints will be assessed with 1 year of follow-up.

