### Sample and study period

The sample will consist of diabetic patients with chronic foot ulcers treated with standard methods, i.e. dressings, debridement, antibiotics and load relief (control group), and to the other group will be added HBOT (HBOT group). The study will be conducted from 2019 to 2020.

The sample size has been calculated based on the formula for comparing two independent groups according to qualitative variables [24], with 95% confidence interval and 80% power. A wound healing rate of 90% was considered achievable for the case group at 1 year, which we expected to be at least 20% higher than in the control group (absolute difference, i.e. no more than a wound healing rate of 70% was expected in the control group). Thus, the total sample size was estimated as 60 patients per group (120 in total).

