### Primary outcome

Wound healing will be assessed by evaluating the diameter of the lesions by specific software and periods, as described in the interventions. The wound healing will be achieved when there is no more skin lesion on the skin and the primary endpoint will be a binary result. The assessor of the primary outcome will be blinded.

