### Data analysis

The collected data will be stored in a Microsoft Excel 2016 spreadsheet format. After checking for errors and inconsistencies, descriptive summaries will be provided by treatment arm, including absolute and relative frequencies and measures of central tendency and variability. We will do regular monitoring, with active search by address and phone to avoid sample loss. We will use the intention-to-treat in the analysis. Blinding will be done for the researcher who will evaluate the final data and for the statistician.

Logistic regression models will be used to assess associations between the categorical variables. Both relative effects (odds ratios) and absolute effects (risk differences) will be presented with corresponding confidence intervals. Student’s *t* test or a similar non-parametric method will be used for the analysis of continuous variables. All examinations will be performed at 5% significance in the IBM SPSS® program, Version 24.0, 2016 (IBM, Armonk, NY, USA).

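### The early ulcer assessments are timed by sessions received in the HBOT arm and by calendar weeks in the control arm, so they are not equivalent unless an unstated common origin and full attendance are assumed

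*Protocol article*

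**What the plan says.** The Interventions section of the protocol article gives the two arms different clocks for the early ulcer assessments.

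- HBOT arm: patients are seen on admission and then "after 10, 20, 30 and 35 HBOT sessions and after 6 months and 1 year".
- Control arm: "the control group will also be assessed at equivalent periods (upon admission, after 2, 4, 6 and 7 weeks", followed by 6 months and 1 year.
- Session frequency: "The HBOT sessions will be conducted 5 days a week".
- Start of treatment: "HBOT sessions will be held 1 week after randomization". No matching shift is given for controls.

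The same section plans a weekly clinical evaluation of the wounds. The Primary outcome section takes over this schedule: "Wound healing will be assessed by evaluating the diameter of the lesions by specific software and periods, as described in the interventions". It makes the primary endpoint binary. The Methods paragraph of the abstract fixes its time: "The primary and secondary endpoints will be assessed with 1 year of follow-up". The Data analysis section states: "We will use the intention-to-treat in the analysis". Fig. 1, the schedule of assessments, is not available in the text reviewed.

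**The concern.** A visit dated by treatment received is not comparable with a visit dated by the calendar. Two things follow.

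First, the arms may have had different amounts of time to heal when they are compared. The difference favours HBOT, because both arms receive standard care throughout and ulcers can improve during the extra days without any effect of oxygen.

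Second, whether and when an HBOT patient is measured depends on how well that patient attends and tolerates treatment. A patient who stops at session 15 has, as the schedule is written, no 20-, 30- or 35-session visit. No control patient can lose a visit in this way. Early data would then be late or missing in one arm only, for reasons linked to treatment, whereas an intention-to-treat comparison needs every randomised patient measured at the same time.

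At stake are the early healing and wound-size comparisons drawn from these visits.

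**Working it through.** **Inputs from the Interventions section.** HBOT visits after sessions 10, 20, 30 and 35; control visits at weeks 2, 4, 6 and 7; 5 sessions a week; first session 1 week after randomisation.

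**Step 1: reproduce the stated equivalence.** Weeks of treatment = sessions / 5, so 10/5, 20/5, 30/5 and 35/5 give 2, 4, 6 and 7. The schedules match when both are counted from the first session and no session is missed.

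**Step 2: count from randomisation, full attendance.** HBOT week = 1 + sessions/5.

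| Visit | HBOT week (nominal) | Control week | Difference |
|---|---|---|---|
| 10 sessions | 3 | 2 | 1 |
| 20 sessions | 5 | 4 | 1 |
| 30 sessions | 7 | 6 | 1 |
| 35 sessions | 8 | 7 | 1 |

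This assumes that control weeks start at randomisation, or at an admission visit close to it.

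**Step 3: exact calendar days.** Take the first session on day 7, sessions on weekdays only, and measurement on the day of the milestone session. For a Monday start, sessions 10, 20, 30 and 35 fall on days 18, 32, 46 and 53. For a start on any other weekday they fall on days 20, 34, 48 and 55. Control visits fall on days 14, 28, 42 and 49. The gap is 4 days or 6 days at every visit. One week is therefore the nominal figure and 4 to 6 days the minimum.

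**Step 4: missed sessions.** The article gives no attendance figure, so a range is assumed. Week of session 35 from randomisation = 1 + 35/(5 × attendance).

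| Assumed attendance | Week of session 35 | Control week |
|---|---|---|
| 90% | 1 + 7.78 = 8.8 | 7 |
| 80% | 1 + 8.75 = 9.75 | 7 |
| 70% | 1 + 10.0 = 11.0 | 7 |

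If control weeks instead start at a matched first-session date, the added 1 disappears, but session 35 still falls 7.8, 8.75 or 10.0 weeks after that date, against 7. The drift does not depend on the origin.

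**Step 5: what the gap is worth if HBOT has no effect.** Assume a constant healing rate that gives 70% healed at 52 weeks, the control figure in the sample size section. Rate = −ln(0.30)/52 = 0.02315 per week; proportion healed at week t = 1 − exp(−0.02315t).

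| Control week | Healed | HBOT week | Healed | Difference (points) |
|---|---|---|---|---|
| 2 | 4.5% | 3 | 6.7% | 2.2 |
| 4 | 8.8% | 5 | 10.9% | 2.1 |
| 6 | 13.0% | 7 | 15.0% | 2.0 |
| 7 | 15.0% | 8 | 16.9% | 1.9 |

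With the 4- to 6-day minimum from step 3, the same formula gives 1.1 to 1.9 points. With 80% attendance, session 35 at week 9.75 gives 20.2% against 15.0%, a difference of 5.2 points.

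**Step 6: the primary endpoint.** The sample size section sets 60 per group, "with 95% confidence interval and 80% power", on healing of 90% against 70% at 1 year. The unpooled two-proportion formula gives (1.960 + 0.842)² × (0.9 × 0.1 + 0.7 × 0.3)/0.2² = 58.9, or 59 per group, close to the stated 60. That calculation uses none of the early visits, and the 1-year visit carries the same calendar label in both arms.

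**The case against.** The strongest reply is that the authors meant matched clocks. The session counts convert exactly to the control weeks, and the text calls the periods equivalent. If control weeks start at a matched first-session date, the offset with full attendance is about zero, and Fig. 1 may say so. This stands as far as it goes: the 1-week offset rests on an inferred origin. It does not answer the drift from missed sessions or the absence of later session-numbered visits in patients who stop.

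It can also be said that weekly evaluation, active follow-up by address and phone, and the 6-month and 1-year visits keep discontinuers under observation. Nothing says that assessment ends when HBOT ends. That is fair, and it makes the fix cheap. But the software measurements are tied to the listed visits, and for these patients those visits have no date. It is also true that no early visit is named as an endpoint time, which limits the consequence.

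Three stronger readings are tempting but unsupported:

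- **At least one extra week in the HBOT arm.** One week is nominal; the calendar minimum is 4 to 6 days, and only on the inferred origin.
- **A biased primary endpoint, because 1 year might run from the end of sessions in the HBOT arm.** The article lists 6 months and 1 year in the same terms for both arms and places the endpoints at 1 year of follow-up. Nothing suggests a different origin in one arm.
- **Unblinding through session-numbered visits.** The article says the primary outcome assessor is blinded and does not say how photographs or measurements are labelled. This is conjecture.

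**Conclusion.** The concern holds for the four early assessments. As written, their timing depends on treatment received in one arm and on the calendar in the other, and the claimed equivalence needs both a common first-session origin, which is not stated, and perfect attendance.

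The timing gap is nominally 1 week if control weeks run from admission or randomisation. It grows with missed sessions on any origin, and later visits are undefined for patients who stop. The spurious advantage is about 2 percentage points per early visit, roughly one patient in 60, and about 5 points at the last session visit if attendance is 80%. These figures rest on the assumed constant healing rate and, for the last, on an assumed attendance as well as the inferred origin.

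The effect falls on early healing and wound-size comparisons, not on the 1-year primary endpoint or the sample size. Severity: moderate, a cheap improvement.

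**What to change.** Date every outcome assessment in both arms from randomisation, at the same calendar times and with one common window. Carry out each assessment regardless of how many sessions have been attended or whether HBOT was stopped. Record session count as exposure data only. Either weeks 2, 4, 6 and 7 or weeks 3, 5, 7 and 8 would serve, so long as both arms share them; state the same origin for the 6-month and 1-year visits.

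The cost is a change of visit dates and labels, mainly in the HBOT arm. Weekly evaluation is already planned, so no extra visits should be needed, and the delivery of HBOT and the sample size are untouched. The downside is that some HBOT assessments will no longer fall on a session milestone.

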### Primary outcome

Wound healing will be assessed by evaluating the diameter of the lesions by specific software and periods, as described in the interventions. The wound healing will be achieved when there is no more skin lesion on the skin and the primary endpoint will be a binary result. The assessor of the primary outcome will be blinded.

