## Background

Globally, more than 400 million adults suffer from diabetes, and the treatment of diabetic foot ulcers is considered as an important public health issue [1]. According to the Ministry of Health of Brazil, the number of diabetic patients in Brazil increased by 61.8% between 2006 and 2016, and the prevalence increased from 5.5 to 8.9%, with more prevalence in women (9.9%) than in men (7.8%). Approximately one in every twenty diabetic patients develops foot ulcers in the first year, and approximately 10% of the patients with ulcers evolve to amputation in this period [2, 3].

Unhealed and infected wounds in diabetic foot cause damage in both tissues and bones, which leads to amputations in 85% of these individuals, and approximately 60% mortality has been reported after amputation during 5 years of follow-up [4–6].

Chronic changes that occur in the feet of diabetic patients, such as peripheral arterial disease, neuropathy with loss of protective sensitivity, deformities and decreased mobility of the feet, are the main challenges in the prevention and treatment of diabetic foot ulcers [7, 8]. The treatment of diabetes and diabetic foot ulcers requires multiple approaches, which involve optimization of glycaemic control, wound care, treatment of infections, load relief and revascularization in ischemic cases [2, 9]. Unfortunately, even with optimal care, the rate of complete healing of the wounds stays approximately 60% per year [2, 10]. Hyperbaric oxygen therapy (HBOT) has been used as an adjuvant therapy for patients with refractory ulcers [11, 12].

Normal wound healing occurs through the ordered and overlapping stages of haemostasis, inflammation, proliferation and tissue remodelling, involving complex molecular and cellular interactions within the wound microenvironment [13]. Regardless of the aetiology of the wound, an adequate condition of the vasculature, including both macrocirculation and microcirculation, is critical for healing. Insufficient perfusion impairs angiogenesis, collagen deposition and epithelialization and may lead to sustained inflammation [14].

Among the advanced therapeutic interventions for wounds, HBOT has the unique ability to improve tissue hypoxia, reduce pathological inflammation and mitigate ischemia-reperfusion injury [15].

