#### Secondary objective

The secondary objective is to assess whether HBOT, along with the standard treatment of chronic diabetic foot ulcers, reduces the number of major (transtibial and transfemoral) and minor amputations (toes and forefoot) and improves the quality of life of these patients, as compared to the standard treatment alone.

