### Secondary outcome

Amputation rates and the reduction of lesions that do not heal will be assessed, with an evaluation of statistical significance between the groups. The evaluation of the domains of the SF-36 quality of life questionnaire will also be done in both groups. The data from this questionnaire upon admission and after 3 months of follow-up will be compared.

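### The primary endpoint does not say how an amputated ulcer is scored; read literally, a closed amputation site counts as healed

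*Protocol article*

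**What the plan says.** The Primary outcome section has lesion diameter measured by software at the scheduled visits and then gives the success rule: "The wound healing will be achieved when there is no more skin lesion on the skin". It adds that "the primary endpoint will be a binary result" and that the assessor is blinded. The Abstract sets assessment of the primary and secondary endpoints at 1 year.

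Amputation appears in three other roles:

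- **As an event during follow-up.** Under Interventions, a vascular surgeon follows patients in both arms, "who will assess the need for surgical procedures (debridement and amputations").
- **As something to be reduced.** The Secondary objective asks whether HBOT "reduces the number of major (transtibial and transfemoral) and minor amputations (toes and forefoot"), and the Hypothesis section expects fewer major amputations.
- **As a separate outcome.** Under Secondary outcome: "Amputation rates and the reduction of lesions that do not heal will be assessed", with a comparison between the groups.

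The Data analysis section specifies intention-to-treat. The article nowhere says how a patient with an amputation is classified on the primary endpoint.

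**The concern.** The success rule depends only on the absence of a lesion, and an ulcer can disappear because it closed or because the tissue bearing it was removed. Once the surgical site has closed, both patients meet the rule. The second has also had the event that the trial hopes to prevent, so one event can be a success on the primary endpoint and a failure on a secondary one.

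If HBOT does reduce amputation, the control arm collects more of these successes and part of the benefit is hidden. Equal amputation among non-healers also narrows the contrast, because the control arm is expected to have more non-healers. If amputations were instead more frequent on HBOT, the rule would push the primary result in favour of HBOT.

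Blinding the assessor does not settle this. The trial is non-blinded, the surgeon is not said to be blinded, and the assessor has no rule for a patient whose ulcer site is no longer there. Intention-to-treat keeps such patients in the analysis, so each must be given a yes or a no.

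**Working it through.** **Inputs from the article**

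- HBOT healing (Sample and study period): "A wound healing rate of 90% was considered achievable for the case group at 1 year".
- Control healing (same section): "no more than a wound healing rate of 70% was expected in the control group".
- 60 patients per arm, 80% power, 95% confidence (same section); 5% significance (Data analysis). Sidedness is not stated; two-sided is assumed.
- Background amputation figure for the first year: "approximately 10% of the patients with ulcers evolve to amputation in this period". This comes from the literature and is not a design input.

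**Step 1. Reproduce the planned sample size.** With p1 = 0.90, p2 = 0.70 and mean 0.80:

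- Pooled formula: n = [1.960 × √(2 × 0.80 × 0.20) + 0.842 × √(0.90 × 0.10 + 0.70 × 0.30)]² / 0.20² = (1.109 + 0.461)² / 0.04 = 61.6, so 62 per arm.
- Unpooled formula: n = (1.960 + 0.842)² × (0.09 + 0.21) / 0.04 = 58.9, so 59 per arm.

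The stated 60 lies between the two, so the sample-size arithmetic is not at fault. Power with 60 per arm is 78.9% by the normal approximation. It is 80.2% by exact enumeration of all pairs of binomial outcomes with the two-sided 5% chi-square test.

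**Step 2. Score closed amputation sites as healed.** Take 90% and 70% as healing without amputation, so that non-healers are 10% and 30%. Let a share f of non-healers in each arm be amputated, with sites closed by 1 year. Then:

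- scored HBOT healing = 0.90 + 0.10f
- scored control healing = 0.70 + 0.30f
- scored difference = 0.20 × (1 − f)

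The Background figure corresponds to f = 1/3 in the control arm, since 0.30 × 1/3 = 10%. The extreme case puts that 10% in the control arm only.

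| Assumption | Amputated and closed, HBOT v control | Scored healing | Exact power, 60 per arm |
|---|---|---|---|
| No amputation scored as healed | 0% v 0% | 90% v 70% | 80% |
| f = 1/10 in each arm | 1% v 3% | 91% v 73% | 74% |
| f = 1/3 in each arm | 3.3% v 10% | 93.3% v 80% | 58% |
| Control arm only | 0% v 10% | 90% v 80% | 33% |

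The normal approximation gives 73.4%, 57.6% and 33.3% for the last three rows.

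**Step 3. Put the loss in patients.** At f = 1/3, about 60 × 10% = 6 control patients and 60 × 3.3% = 2 HBOT patients change category. That is enough to cut the expected difference from 20 to 13.3 points. By the pooled formula, 80% power for 93.3% against 80% would need 101 per arm.

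**The case against.** The strongest reply is that the article never calls amputation a success. The success rule follows a sentence about measuring the lesions, the objectives speak of ulcers healing, and amputation rates are listed apart from lesions that do not heal. A sensible assessor might therefore record an amputated ulcer as not healed. This stands in part: a reader might infer that the trial deliberately credits amputation as healing, and the text does not support that. It supports only that the definition, applied as worded, permits it.

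A reader might also infer that the misclassification is bound to happen, or that power will fall to 33%. Neither follows. The surgeon only assesses the need for amputation, and a surgical site still open at 1 year is itself a lesion and fails the rule. The 10% describes ulcer patients in general, whereas this trial enrols Wagner grades 2 to 4 and excludes patients with two absent distal pulses, so the rate here could differ in either direction. The 33% needs every amputation to fall in the control arm, and the milder case costs only about 6 points of power. A false benefit for HBOT is possible in principle, but nothing in the article puts a figure on it. Nor does the article rank its secondary outcomes, so amputation should not be called the main one.

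The last reply is that scoring rules of this kind belong in a fuller protocol or analysis plan, which is not shown. For a detail merely left out, that would be enough. Here the article states the success rule itself, and a plan that scored amputation as failure would add a condition missing from that rule. Reporting amputations separately would make a divergence visible, but would not correct the primary comparison.

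**Conclusion.** The point holds as a badly fixed definition. The stated rule does not separate an ulcer that closed from one that was removed, and its literal reading conflicts in direction with the secondary objective. Intent to count amputation as success is not shown.

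The effect is a conditional range: power of about 74% in the mild case, 58% at the Background rate with the same share of non-healers amputated in each arm, and 33% in the extreme, against 80% as planned. All three assume that the planning rates mean healing without amputation, that amputees would otherwise be unhealed, and that all sites close by 1 year. Sites still open at 1 year would reduce the effect. The article gives no arm-specific amputation rates with which to choose within the range.

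Severity: should be fixed. Confidence: moderate, because the wording can be read otherwise and a scoring rule may exist elsewhere.

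**What to change.** Before outcome data are examined, reword the primary endpoint along these lines: *complete closure of the index ulcer at the 1-year visit, without amputation at or above the level of that ulcer since randomisation; a patient with such an amputation is scored as not healed.* Add a sensitivity analysis that counts healing after minor amputation as healed. Scoring every such amputation as failure is one defensible convention that the article does not dictate, and the sensitivity analysis shows whether the conclusion depends on it. If an analysis plan already holds a scoring rule, the protocol definition should be brought into line with it.

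The cost is a sentence or two. Amputations are already recorded as a secondary outcome, though the level relative to the index ulcer and the date must be available. If 90% and 70% were meant as healing without amputation, the sample size is unchanged. Observed healing rates may be slightly lower than under the present wording. Fixing the rule in advance matters because choosing it afterwards could change the primary result.
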